**Fig. 1 Fig1:**
[figure not shown]
Trial Design

### Sample size estimation

The estimation of sample size was done considering the study design as two-parallel arm cluster RCT [26]. We assumed that 12% of the child births have been attended by a skilled birth attendant (SBA) at baseline in both arms and this rate will increase to 32% post- intervention in the intervention arm. 20% as the minimum difference between the two groups we would like to see after intervention with 0.80 power and 0.05 level of significance, and to account for intra-cluster correlation by taking the design effect of 2.29 for delivery attended by SBA, an adjusted sample size of 147 pregnant women in each arm is required for the study [4, 24]. With allowable 20% potential attrition, the final sample size is 177 for each arm. Thus, 354 pregnant women are estimated to be included in a trial. This number would be sufficient to detect a change in the effect sizes over a follow-up period in the intervention group as compared to control group. The study area consisted of 67,625populations (male/female ratio = 100:94) and the reported birth rate are 25.5 per 1000 per year [4], which gives an estimated 1724 expected pregnant women. Since, this study will consider the pregnant women in their second trimester, around 431 (=1724 × 0. 25) pregnant woman would be available at any point of time during a year, which is sufficient number for our study.

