**Method/design:**

MATRI-SUMAN is a 12-month cluster randomized controlled trial (RCT). The trial involves pregnant women from 52 clusters of six village development committees (VDCs) covering 66,000 populations of Dhanusha district of Nepal. In the intervention clusters, Female Community Health Volunteers (FCHVs) will receive capacity development skills through reinforcement training, supervision and monitoring skills for the promotion of health seeking behaviour among pregnant women and study participants will receive periodic promotional text messaging service about MCH components through mobile phones. A sample of 354with equal numbers in each study arm is estimated using power calculation formula. The primary outcomes of this study are the rate of utilization of skilled birth attendants and consumption of a specified diversified meal. The secondary outcomes are: four antenatal (ANC) visits, weight gain of women during pregnancy, delivery of a baby at the health facility, postnatal care (PNC) visits, positive changes in child feeding practices among mothers, performance of FCHVs in MCH service utilization.

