### Data management and analysis plan

Data entry will be performed in EpiData software version 3.1 and then it will be transferred to STATA software (Version 13.0) where all statistical analyses will be performed. The logistic regression model will be used to assess primary and secondary outcomes of the intervention. The independent t-test will be used to compare mean of different variables between the intervention and control groups. Chi-square test will be used to investigate the association between categorical variables in intervention and control groups. Within group analysis will also be done for outcomes whether it is attributed to either text message or capacity building or both.

For the repeated anthropometric measurement, biochemical test and dietary measures, we will use generalized estimating equation (GEE) and mixed model analysis to evaluate the effects of the intervention. The analysis will adjust for potential confounders for changes in weight gain and haemoglobin including baseline socio-demographic characteristics. We will also evaluate the possible interactions between the intervention indicators and participant attributes to assess the effect of intervention. Data will be analysed by ‘intention-to-treat’ principle.

Multiple imputations will be performed to account for missing data. Results will be expressed as odds ratios (ORs) with 95% confidence intervals for primary and secondary binary outcomes. Exploratory analysis will also be carried out on participant’s sub-groups to address heterogeneity. All test will be two-tailed and *p*-value will be set at < 0.05 for statistical significance.

All the FGDs will be recorded in a voice recorder. A coding framework will be prepared based on FGDs guideline. Transcription of data will be done in Nepali (National language), and then will be translated to English. Two researchers will be involved separately for coding based on pre-identified theme in the evaluation framework. Coding will be compared for consistency. The analysis will be done manually and no other software will be used for qualitative data analysis.

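### The 177 women per arm keep the required 147 only up to about 17% attrition, not the stated 20%

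*Protocol article*

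**What the plan says.** All the figures are in the protocol article, under Sample size estimation.

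- Control rate: "We assumed that 12% of the child births have been attended by a skilled birth attendant (SBA) at baseline in both arms".
- Intervention rate: "this rate will increase to 32% post- intervention in the intervention arm".
- Error rates: "with 0.80 power and 0.05 level of significance". The data management and analysis section adds "All test will be two-tailed".
- Clustering: "taking the design effect of 2.29 for delivery attended by SBA".
- Requirement after clustering: "an adjusted sample size of 147 pregnant women in each arm is required for the study".
- Attrition step: "With allowable 20% potential attrition, the final sample size is 177 for each arm".

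The section doubles 177 to 354, and the abstract repeats that total: "A sample of 354with equal numbers in each study arm is estimated using power calculation formula". The formula for the attrition step is not written out.

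**The concern.** The section gives 147 per arm as the number required and 177 as the number that protects it against 20% loss. Both figures are printed, so they can be checked against each other without knowing which formula produced 147. Taking 20% away from 177 does not return 147. Adding 20% to the requirement is a common shortcut, and it always falls short because the loss applies to the larger, enrolled number.

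At stake is whether the stated combination of 354 women, 20% attrition and 147 evaluable women per arm is true as written. The article also offers itself as guidance to future researchers, so the step could be copied.

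**Working it through.** **Inputs** (Sample size estimation, except where noted): p1 = 0.12; p2 = 0.32; difference 0.20; power 0.80; alpha 0.05, two-sided (Data management and analysis plan); design effect 2.29; required 147 per arm; attrition 20%; final 177 per arm. There are 26 clusters per arm (Matching).

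**Step 1: reproduce 147.** Two proportions, normal approximation, unpooled variance:

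- n = (1.960 + 0.842)² × (0.12 × 0.88 + 0.32 × 0.68) / 0.20² = 7.849 × 0.3232 / 0.04 = 63.42, rounded up to 64
- 64 × 2.29 = 146.56, rounded up to 147. This matches.

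The article names no formula, so the unpooled form is inferred from the match. The pooled form gives 67 × 2.29 = 153.4, and with a continuity correction 76 × 2.29 = 174.0. Neither gives 147.

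**Step 2: reproduce 177.**

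- 147 × 1.20 = 176.4, rounded up to 177. This matches exactly.

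**Step 3: test it against 20% loss.**

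- 177 × 0.80 = 141.6, which is 5.4 short of 147
- 147 / 0.80 = 183.75, rounded up to 184; 2 × 184 = 368
- 184 × 0.80 = 147.2, which keeps 147
- Shortfall: 184 − 177 = 7 per arm; 368 − 354 = 14 in total
- Loss that 177 can absorb: 1 − 147/177 = 0.169, or 16.9%

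**Step 4: power at 20% loss, design effect held at 2.29.** Power = Φ(0.20 / √(0.3232 / n_eff) − 1.960), with n_eff = women per arm / 2.29.

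| Women per arm | n_eff | Power |
|---|---|---|
| 147 | 64.19 | 80.5% |
| 141.6 | 61.83 | 79.0% |

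**Step 5: power at 20% loss if the design effect shrinks with cluster size.** Here the design effect is 1 + (m − 1) × ICC, where m is the number of women per cluster. The article does not say which cluster size 2.29 belongs to, so two readings are shown as assumptions. After 20% loss, m = 141.6/26 = 5.45.

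| Assumed origin of 2.29 | m | Implied ICC = 1.29/(m − 1) | Design effect at m = 5.45 | Power at 141.6 |
|---|---|---|---|---|
| 147 per arm | 147/26 = 5.65 | 0.277 | 2.23 | 80.0% |
| 177 per arm | 177/26 = 6.81 | 0.222 | 1.99 | 84.4% |

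**The case against.** The strongest reply is that nothing of substance is lost, and several parts of it stand.

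- **Power.** A reader might infer that the trial is underpowered at the attrition it allows for. The article does not support that as a firm statement. The 79.0% depends on keeping the design effect at 2.29 while the clusters get smaller. Under the two cluster-size readings above, power at 20% loss is 80.0% or 84.4%. Replacing the normal reference with a t reference based on the number of clusters would give a lower figure. However, the article states no such reference, and it gives only about 79% even at the full 147, so most of that drop comes from the change of method and not from the attrition step.
- **Rounding.** The 147 was rounded up twice. The unrounded requirement is 63.42 × 2.29 = 145.2, and against that 177 tolerates 1 − 145.2/177 = 17.9% loss. This narrows the gap but does not close it, since 141.6 is still below 145.2.
- **Recruitment.** The article describes enumerating all eligible second-trimester women in the 52 clusters and including them all, with about 431 expected to be available. The 354 is therefore closer to a feasibility check than a cap, and 368 would also have passed it. A reader might infer that too few women were enrolled; the article does not show that.
- **Meaning of attrition.** One could read the 20% as a share of the 147 and not of those enrolled. That reading reconciles the numbers, but the 30 women it allows to be lost are 30/177 = 16.9% of those enrolled. The usual meaning of attrition is a share of those enrolled, and the sentence gives no sign of another.

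None of this makes the printed sentence correct. It limits the consequence.

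**Conclusion.** The point holds as an arithmetic error in a stated figure. On the article's own numbers, 177 per arm does not retain 147 after 20% loss; 184 per arm would be needed, and 354 women tolerate 16.9%. This conclusion rests only on the printed 147, 177 and 20%, and on attrition meaning a proportion of women enrolled.

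The size is small: 7 women per arm and, with the design effect fixed at 2.29 and the unpooled formula, about one point below the stated 0.80 power. That power figure is conditional and should be quoted only with its condition. The error touches neither the design nor the analysis. The article reports the trial as completed, so raising the target is no longer an option.

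**What to change.** Replace the attrition sentence with wording such as: *354 women (177 per arm) retain the required 147 per arm with up to about 17% attrition; 20% attrition would have required 184 per arm (368 in total).* If power is quoted, add: *at 20% attrition power is about 79%, holding the design effect at 2.29.* The total of 354 in the abstract can stay.

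The cost is one corrected sentence and a slightly less favourable stated tolerance. Enrolment, conduct and analysis are unchanged.

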### Sampling technique

We employed multi-stage cluster sampling. First, two health facilities (consisting of one primary health care centre and one health post) catchment area of Dhanusha district has been selected purposefully. We selected these health facilities because there have been no MCH-related services from other organizations before, but the governmental. Furthermore, no research work has been conducted yet relating to this field.

Second, six VDCs have been selected in the catchment area of these two health care facilities by stratified random sampling technique. The population of each VDC in the catchment area range from 3500 to 19,000. Therefore, VDCs in both health care facilities catchment areas have been stratified into three strata based on population size (< 5000, 5000–10,000, and > 10,000), forming a total of six strata. One VDC has been randomly selected from each stratum [24, 25]. Third, those selected six VDCs comprised of 54 wards (here we called cluster for our study) where two of them are excluded as these wards are situated in the town area. The reminder 52 clusters have been selected for a trial. Finally, the complete enumeration of all households with pregnant women in their 2nd trimester from these clusters has been carried out.

### Identification and recruitment of participants

All households with pregnant women in 52 clusters have been identified and screened applying inclusion and exclusion criteria. The identification of pregnant women has been made with the help of FCHVs’ antenatal registers. Pregnant women from each household in have been registered by FCHVs in their respective ward. All pregnant women with gestational period between 13 to 28 weeks are included in the study. Each household is coded and marked in the outside wall with a visible unique serial number to track participants during follow-up period.

The baseline information of these pregnant women was collected between July and September 2015. Selection of participants has been done by trained female research assistants (FRA), who are fluent in both Nepali and Maithili languages. Written informed consent have been taken from each participant who are willing to participate in the study. Participants are informed about the purpose of the study, advantages and any potential harms arising from a study. Head of the family, usually husband or close relatives of the relevant participants, were also informed about the study. For any adverse event or inquiry by the participants will be entertained or clarified.

### Matching

Before baseline data collection, pre-trial inventory on antenatal, delivery and postnatal care, and number of pregnancies in the study area have been obtained from respective health facilities and FCHVs’ records. We have formed matched pair of clusters consulting with village secretary, chairman of the ward and FCHV of the respective ward. There are three criteria for matching: approximately equal numbers of pregnant women in the cluster; similar or predominant ethnic group distribution in each cluster; and proportionate SBA utilization rate across the cluster. The matched pair of cluster is made within each VDC. As there are nine wards in each VDC, an odd number of clusters in the VDC have been matched with odd number of cluster with other VDC. We have selected 26 matched pairs from52 clusters of the study area. Finally, 26 pairs of clusters were randomized into intervention and control arms, each arm holding 26 clusters.

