### Randomization

Twenty-six pairs of matched clusters have been ranked from the top best matched to the bottom matched based on matching criteria. Within each pair, the random allocation rule has been used to assign either to the intervention group or control group (Additional file 1). There is no blinding of the researchers and participants in the study due to the nature of the intervention and ethical reasons. Data collectors during follow-up will be blinded to allocation.

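### Wards were randomised within 26 matched pairs, but the named between-arm tests use neither ward nor pair: omitting the ward understates error, and omitting the pair alone only forgoes efficiency

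*Protocol article*

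**What the plan says.** The Matching section describes 52 wards grouped on three criteria: number of pregnant women, ethnic composition, and "proportionate SBA utilization rate across the cluster". It states "We have selected 26 matched pairs" and concludes: "Finally, 26 pairs of clusters were randomized into intervention and control arms, each arm holding 26 clusters". The Randomization section confirms the restriction: "Within each pair, the random allocation rule has been used to assign either to the intervention group or control group".

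The Data management and analysis plan section names these methods:

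- Primary and secondary outcomes: "The logistic regression model will be used to assess primary and secondary outcomes of the intervention".
- Means: "The independent t-test will be used to compare mean of different variables between the intervention and control groups".
- Categorical variables: "Chi-square test will be used to investigate the association between categorical variables in intervention and control groups".
- Repeated anthropometric, biochemical and dietary measures: "we will use generalized estimating equation (GEE) and mixed model analysis to evaluate the effects of the intervention".

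The only covariate adjustment described is for potential confounders of weight gain and haemoglobin, including baseline socio-demographic characteristics. Neither the ward nor the pair is mentioned in any analysis. The sample size section does allow for clustering, with a design effect of 2.29 for SBA delivery. It takes no credit for matching.

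**The concern.** Allocation was restricted twice: whole wards were allocated, and one ward per pair went to each arm. The sampling variance of the treatment comparison follows from both restrictions. The independent t-test, the chi-square test and an ordinary logistic regression treat every woman as an independent observation in one of two unrelated groups.

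The two omissions pull in opposite directions. Leaving out the ward makes standard errors too small and produces false positives. Leaving out the pair, once the ward is handled, makes standard errors too large, because between-pair variance that the design removed stays in the error term. Any statement that the standard errors do not fit the design therefore has to say which omission is meant.

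**Working it through.** **Inputs.** From the article: SBA rates of 12% and 32%, power 0.80, two-sided 5% level, design effect (DE) 2.29, 147 women per arm before attrition, 26 pairs. Not in the article: r, the within-pair correlation of ward-level outcomes. It is assumed and varied from 0 to 0.5.

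**1. The plan's own figure.** n = (1.96 + 0.8416)² × (0.12×0.88 + 0.32×0.68) / 0.20² = 63.4, rounded up to 64. Then 64 × 2.29 = 146.6, rounded up to 147. The published figure reproduces, so the trial was sized for a variance inflated 2.29-fold.

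**2. Tests as written (no ward, no pair).** The true variance is about DE × (1 − r) times the variance the tests use.

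- At r = 0 the standard error is too small by √2.29 = 1.51. The true error is 2 × [1 − Φ(1.96/1.51)] = 19.5%.
- With matching, the true error is 2 × [1 − Φ(1.96/√(2.29(1 − r)))]. This gives 17% at r = 0.1, 15% at 0.2, 12% at 0.3 and 7% at 0.5.

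**3. Ward handled, pair ignored or used.** The unpaired ward-level t-test has 52 − 2 = 50 degrees of freedom and the paired test 26 − 1 = 25. The effect is calibrated so that the unpaired test has 80% power when r = 0 (non-centrality 2.857). Pairing multiplies the standard error by √(1 − r), so paired power comes from the non-central t with 25 df and non-centrality 2.857/√(1 − r). Unpaired power and type I error come from simulating 26 normally distributed ward pairs.

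| Assumed r | Paired power | Unpaired power | Unpaired type I error | Unpaired SE too wide by |
|---|---|---|---|---|
| 0 | 78% | 80% | 5.0% | 0% |
| 0.1 | 82% | 81% | 4.0% | 5% |
| 0.2 | 87% | 83% | 2.9% | 12% |
| 0.3 | 91% | 84% | 2.0% | 20% |
| 0.5 | 97% | 88% | 0.7% | 41% |

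The last column is 1/√(1 − r) − 1.

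**4. Break-even.** Equating t(50 df) × SE with t(25 df) × SE × √(1 − r) gives r = 1 − (2.0086/2.0595)² = 0.049. Pairing starts to pay somewhere around 0.05 to 0.1.

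**5. How large r could be.** Suppose DE = 2.29 applies at 147/26 = 5.65 to 177/26 = 6.81 women per ward. The implied intra-cluster correlation is 1.29/4.65 = 0.28 to 1.29/5.81 = 0.22. True between-ward variance is then 5.65 × 0.277/2.29 = 68% to 6.81 × 0.222/2.29 = 66% of the variance of a ward mean. Even perfect matching could not take r above about 0.67, and r = 0.5 would need matching to capture about three quarters of the true between-ward variance. The upper rows of the table are optimistic.

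**The case against.** The strongest reply is that ignoring the match is legitimate. With wards handled as clusters, an unpaired analysis keeps type I error at or below 5%, and the sample size took no credit for matching. In the table the unpaired power never falls below the planned 80%. This stands: the pair-only part is a loss of extra efficiency, about 1 point at r = 0.1 and 4 points at r = 0.2. The article does not, however, say that it chose to break the match, and with 25 df left the price of keeping it is small.

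A second reply is that a journal article leaves model terms to a fuller plan, that logistic regression does not exclude such terms, and that the t-test and chi-square are not tied explicitly to the primary outcomes. The GEE and mixed models, which cover the repeated dietary measures, could also carry ward and pair terms. This is partly right. But the article goes further than silence: it names tests for independent groups as comparisons between the arms, and SBA use at delivery is a single binary outcome that falls under the logistic regression, not the repeated-measures models.

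Third, r is unknown. Some leftover wards were paired across village development committees, and the pairs were ranked from best to worst, so match quality varied. Diet, the other primary outcome, was not a matching criterion. All of this stands and limits what can be claimed about size.

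A reader might infer from the ignored pairs that the planned confidence intervals are too wide. The article does not support that, because this direction holds only after the ward has been accounted for, and the named tests do not do so. As written they err the other way.

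**Conclusion.** The mismatch between the allocation and the named tests is real, and it has two parts of unequal weight.

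- **As written**, the missing ward dominates: standard errors are about 1.5 times too small, and a nominal 5% test has a true error of up to about 20%. This rests on the protocol's own design effect, given for SBA delivery only. It falls to about 15% at r = 0.2 and 7% at r = 0.5.
- **If the ward is handled and the pair is not**, the result is valid but conservative. The forgone power runs from about 1 point (r = 0.1) to about 9 points (r = 0.5), on an r that the article does not give.

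The gain from using the pair is most plausible for SBA use, because wards were matched on its rate before the trial, and less certain for diet. Nothing here shows that ignoring the pairs by itself creates false positives or takes power below the planned 80%.

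**What to change.** In the Data management and analysis plan section, state that between-arm analyses of the primary and secondary outcomes account for the ward as cluster and the matched pair as stratum. One form that keeps the odds ratios the article commits to is a logistic model with ward clustering and a pair term. If that model is unstable, support it with a within-pair permutation p-value or a ward-level paired analysis. A paired risk difference alone would change the reported effect measure. Carry the same two terms into the GEE and mixed models for repeated measures. Do not use the individual-level independent t-test and chi-square as between-arm outcome tests.

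The cost is one or two sentences and no new data, because pair membership follows from the allocation. Pairing loses about 2 points of power if matching was uninformative (78% against 80% at r = 0). A model with both terms may be hard to fit: at 12%, 147 control women yield about 147 × 0.12 = 18 events over 26 wards. Since the Trial status section reports the trial as completed, the change would have to be reported as one made after completion unless a fuller plan already contains it.
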